### Provisions for post-trial care {30}

There will be no provisions for post-trial care, including continuation of treatment with teriparatide. Teriparatide is not currently licensed for the treatment of stress fractures and cannot be prescribed outside of the trial. The Ministry of Defence maintains an arrangement for the payment of no-fault compensation to individuals who suffer illness, injury or death as a direct result of participating as a volunteer in research conducted on their behalf and given favourable opinion by the Ministry of Defence Research Ethics Committee (MODREC). As a trial sponsored by an NHS organisation, NHS insurance for negligent harm covers sponsor activities and those of participating NHS trusts. Non-negligent harm does not include side effects, which are listed in the trial protocol and participant information sheet. Under the terms of the no-fault compensation scheme, the Ministry of Defence insures against side effects that are listed in the trial protocol and participant information sheet, as well as unknown side effects that may develop at a later date.

### Outcomes {12}

#### Primary outcome

The primary outcome will be the improvement in radiological healing of lower body stress fractures by two Fredericson grades or more, or reduction in grade to zero, 8 weeks after randomisation. Radiological healing will be assessed using T1 and fluid sensitive (fat suppressed T2W or short tau inversion recovery) MRI sequences and the Fredericson grading system (39, 40). All MRI scans will be assessed independently by two musculoskeletal consultant radiologists blind to the randomisation outcome. Assessors will be notified of any between-assessor grading discrepancies and will be asked to agree a consensus grade.

#### Secondary outcomes

##### Time to radiological healing

Radiological healing will be assessed at weeks 8, 10, 12, 14, 16, 20 and 24 by MRI, with a Fredericson grade zero classified as healed [39, 40]. The time from randomisation to radiological healing will be analysed. No further MRI scans will be necessary when fractures have healed, hence the total number of MRI scans a participant will undergo will vary. All MRI scans will be conducted and graded using the same methodology used for the primary outcome.

##### Time to clinical healing

Clinical healing assessments will commence twice weekly after a participant has been classified as radiologically healed, using a protocol based on the index developed by Beck et al. 2012 [41]. A clinical severity score will be calculated from seven sign and symptom scores: (i) pain during daily activities; (ii) night pain; pain when (iii) running and (iv) hopping; and (v) local tenderness, (vi) pain during percussion, and (vii) local swelling of soft tissue, each at the site of the stress fracture. Clinical assessments will cease when a clinical severity score of zero (i.e. healed) has been achieved. The time from randomisation to clinical healing will be analysed.

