### Intervention description {11a}

All participants will receive usual Army standard care. According to standard Army procedures, all recruits will be taken out of training on confirmation of their injury and referred for extended rehabilitation in a rehabilitation platoon. Recruits may be sent on sick leave, with the duration determined according to the severity of their injury and symptoms. Early rehabilitation will concentrate on upper body, non-impact cardiovascular work and swimming/deep water running. Exercise interventions will aim to maintain cardiovascular fitness using non-impact activities and to maintain strength as pain allows. Once rehabilitation is complete and a recruit is fully fit, they will be graded as fit to return to training. The final functional test before a decision to return to training is made will be the successful completion of a weighted distance march without symptoms, at a level appropriate to the week of training they are returning to. A review by an Army exercise rehabilitation instructor, physiotherapist and general practitioner will be required to determine if a recruit is ready to return to training. The rehabilitation team will be informed of a recruit’s participation in the study, but this will not affect their treatment or rehabilitation programme in any way.

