**Fig. 2 Fig2:**
[figure not shown]
Schedule of study enrolment, interventions and assessments. ^1^Intervention and assessments to continue after week 16 only where fractures are unhealed at week 16; ^2^Serum 25-hydroxyvitamin D < 30 nmol/L, deficient; ≥30 nmol/L, not deficient; ^3^Daily subcutaneous injection (20 μg/day); ^4^Magnetic resonance imaging (MRI) scans to cease when fracture is radiologically healed; ^5^Clinical assessments twice weekly after fracture is radiologically healed, and to cease when fracture is clinically healed; ^6^Weekly visual analogue scale; ^7^Short Form (36) Health Survey; ^8^Adverse events recorded for 4 weeks after participant’s final study visit (i.e. until weeks 20 or 28). ^9^Safety and research blood biochemistry; ^10^Safety and research urine biochemistry; ^11^Dual-energy X-ray absorptiometry (DXA) scan of the lumbar spine and hips (allocation and week 16 only); peripheral quantitative computed tomography (pQCT) scan of the diaphyseal tibia; and high-resolution pQCT (HR-pQCT) scan of the metaphyseal tibia and radius; ^12^Accelerometer worn 24 h/day and replaced four-weekly; ^13^Review of Army medical records for 5 years after participant’s final study visit; ^14^Columbia-Suicide Severity Scale for all at allocation, and four-weekly for participants allocated to the intervention arm; ^15^Review of Army fitness records; ^16^Pregnancy test for all at allocation, week 16 and 24, and four-weekly for participants allocated to the intervention arm

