The recovery of participants’ physical function and health will be assessed using a variety of methods. Using a clinical severity score to assess clinical healing once a fracture is radiologically healed will enable a standardised assessment of physical function to be made [41]. In addition, the time to discharge from physical rehabilitation will provide a measure of physical function and readiness to return to training. The time to discharge from physical rehabilitation will be affected by confounding variables e.g. (i) the physical demands of the training course the participant is re-joining, determined by the week of training at the time of injury, and the physical intensity of their regiment’s training programme; and (ii) the participant’s compliance to, and engagement with, their rehabilitation programme. Although reliant on self-report, the pain visual analogue scale and SF-36 are relatively easy to complete and will add minimal additional burden to participants. The visual analogue scale has been shown to be a valid and reliable tool to assess pain [42, 43] and will be interpreted alongside the participant’s record of analgesic use. The widely used SF-36 will provide a valid and reliable measure of health-related quality of life, functional health and wellbeing [44, 45]. The inclusion of assessments of blood and urine biochemistry; bone density and morphology; and physical activity levels will provide an insight into the mechanisms underlying the hypothesised beneficial effect of teriparatide on stress fracture healing. Participants’ alcohol consumption, smoking habits and physical fitness (confounding factors for skeletal health [46]) will be recorded so the possible effect of these variables on study outcomes can be analysed.

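### Time to clinical healing is scored only once the MRI reads grade zero, so a drug effect on the MRI alone can appear as faster clinical healing

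*Protocol article*

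**What the plan says.** Objectives {7} lists time to radiological healing and time to clinical healing as separate secondary objectives. The section on time to clinical healing sets the start of scoring: "Clinical healing assessments will commence twice weekly after a participant has been classified as radiologically healed". It ends scoring at a severity score of zero and counts time from randomisation. Fig. 1 (footnote 10) and Fig. 2 (footnote 5) give the same rule, the latter as "Clinical assessments twice weekly after fracture is radiologically healed, and to cease when fracture is clinically healed". The Discussion repeats it: "Using a clinical severity score to assess clinical healing once a fracture is radiologically healed".

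The section on time to radiological healing fixes the MRI visits, the first at week 8 and the last at week 24, and treats only a complete return to normal as success, "with a Fredericson grade zero classified as healed".

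On length of follow-up, Fig. 2 footnote 1 reads "Intervention and assessments to continue after week 16 only where fractures are unhealed at week 16". Footnote 8 records adverse events for four weeks after the "final study visit (i.e. until weeks 20 or 28"), which puts the final visit at week 16 or week 24 (20 − 4, 28 − 4).

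Discharge from rehabilitation is decided separately. Its last functional test is "successful completion of a weighted distance march without symptoms" (Intervention description {11a}), and study MRI results reach the rehabilitation staff only after that decision is recorded (Protocol amendments).

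**The concern.** Before the MRI reads zero, no clinical score exists. A recruit who is free of symptoms at week 6 but whose MRI clears at week 14 is recorded as clinically healed at about week 14. The same recruit could pass the weighted march and be discharged while still counted as not clinically healed.

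An outcome built this way carries any between-arm difference in MRI clearance into the clinical result. The article presents the score as a standardised assessment of physical function, so a reader of the results would take a shorter time to clinical healing as evidence that recruits recover sooner. The plan, followed exactly, could yield that conclusion when only the imaging differs. Scores not collected before MRI healing cannot be recovered later by any analysis.

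**Working it through.** **1. The rule as a formula.** Let M be the first scheduled MRI visit reading grade zero (weeks 8, 10, 12, 14, 16, 20, 24) and C the time at which symptoms have resolved. The recorded time is max(M, C), rounded up to the next twice-weekly assessment. Two cases by hand:
- C = 6: M = 8 gives 8 and M = 14 gives 14. The clinical course is the same and the recorded times differ by six weeks.
- C = 15: M = 8 and M = 14 both give 15. The MRI has no influence.

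The distortion therefore depends on how early symptoms resolve relative to MRI clearance. The article does not give this.

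**2. The plan's own figures.** The article gives no figure for this outcome. Its sample-size figures, used as inputs below, reproduce closely. For 43% against 71%, two-sided 5%, 80% power, the chi-squared formula gives 48 per arm without and 55 per arm with continuity correction (stated: 54). Power at 54 per arm with the correction is 79.3% (stated: 80%). 54 / 0.80 = 67.5, so 68 per arm and 136 in total, as stated. The odds ratio is (0.71/0.29)/(0.43/0.57) = 3.25 (stated: 3.23).

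**3. Simulation with no clinical effect.** There were 54 participants per arm and 500 trials per setting (Monte Carlo standard error at most √(0.25/500) = 2.2 points), analysed by log-rank test. Symptom time has the same distribution in both arms; only MRI clearance differs. Assumptions not in the article:
- MRI time is Weibull with shape 1.5 and scale 8/(−ln(1 − p))^(1/1.5), where p is the week-8 grade-zero rate.
- p is 43% v 71%, or 20% v 40%. The article's 43% and 71% also count two-grade improvements, so they overstate grade zero; the lower pair allows for this.
- Symptom time is log-normal, log SD 0.5, with median 4, 8, 12 or 16 weeks.
- Correlation between MRI and symptom times is 0 or 0.5 (this gives the ranges in the cells).
- Follow-up ends at week 16 if the MRI has cleared by then, otherwise at week 24.

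Share of trials with a significant result favouring teriparatide (nominal 2.5%):

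| Median symptom time | Grade zero 43% v 71% | Grade zero 20% v 40% |
|---|---|---|
| 4 weeks | 96–98% | 96–97% |
| 8 weeks | 69–77% | 92–93% |
| 12 weeks | 17–38% | 73–82% |
| 16 weeks | 8–18% | 32–52% |

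**4. Which feature causes it.**
- Scoring in everyone from randomisation to week 24, whatever the MRI shows: about 1–4% in every setting.
- MRI condition kept, but everyone followed to week 24: 9–99%, much the same or higher.

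The MRI condition is the cause, not the week-16 stop.

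**5. What the week-16 stop does, on the radiological reading.** It loses events. At a 12-week symptom median, 62–74% of participants have a recorded event, against 74–90% with follow-up to week 24. At 16 weeks the figures are 46–53% against 64–78%. A participant first MRI-healed at week 16 has almost no assessment window, and the censoring date depends on when the MRI cleared.

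**6. How closely the outcome tracks the MRI.** With the week-16 stop, 32–99% of recorded events fall on the first possible visit, and the rank correlation with MRI time is 0.57–1.00.

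**The case against.** The rule is explicit and stated the same way throughout, so an attentive reader can see that the outcome needs both MRI and clinical healing. It is one of six secondary objectives. Weekly pain, SF-36 and time to discharge do not depend on the MRI, and the hypotheses in Objectives {7} concern radiological healing, pain and return to training. The recruit who passes the march before the MRI clears is captured by time to discharge. All of this stands, and it limits what is at stake. It does not make the outcome, under its present name, a measure of clinical recovery.

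Four stronger readings are tempting and are not supported:

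- *The outcome mostly re-measures the MRI.* This is true if symptoms usually clear before grade zero, but not across the range: the share of events on the first possible visit falls to 32%. Background and rationale {6a} gives rehabilitation often beyond 80 days (11.4 weeks) and an average return to training for athletes of 61 to 153 days (8.7 to 21.9 weeks). These are not symptom times, but they caution against relying on the 4-week row.
- *The week-16 stop produces the false benefit.* Step 4 shows that it does not. Participants whose MRI first clears at week 24, or never clears, also lack clinical assessment for reasons unrelated to that stop.
- *Fig. 2 ends clinical assessment at week 16 for everyone whose MRI has healed.* Footnote 1 says only 'unhealed'. The section on time to clinical healing also calls a severity score of zero healed, and footnote 5 ends assessments only at clinical healing. Footnote 8 fits either reading.
- *The trial cannot show a clinical benefit.* The outcomes that do not depend on the MRI can still do so.

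**Conclusion.** The concern holds in limited form. The recorded time is the later of MRI clearance and symptom resolution, so this outcome alone cannot distinguish a drug that clears the MRI sooner from one that helps recruits recover sooner. With no clinical effect, the chance of a significant result for teriparatide was 8–98% in the settings tried, against 2.5%. The direction was the same in all of them. The size rests on assumed symptom-recovery times, grade-zero rates and distributions that the article does not supply, so no single figure should be quoted as the trial's error rate.

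The meaning of 'unhealed' in Fig. 2 is a separate ambiguity. On the radiological reading it costs events and ties censoring to the MRI, but it does not create the false benefit. The primary outcome and the sample size are not affected.

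**What to change.** Change the section on time to clinical healing, and Figs 1 and 2 to match, in one of two ways.

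1. **Score everyone, whatever the MRI grade.** Define the outcome on the items of the index that the clinical team judges can be scored in all participants, at visits already scheduled. The contacts held at least every four weeks (section {18b}) suit this better than the MRI visits, which stop once the MRI has healed. If scoring times and follow-up are the same whatever the MRI shows, equal symptom recovery gives equal recorded times in both arms. The simulation tested twice-weekly scoring to week 24, not this coarser schedule. Cost: a short extra score at existing contacts, coarser timing, possibly fewer items than the full index, and no information before the first such visit. Longer follow-up for everyone is not needed to remove the bias.

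2. **If scoring must wait for the MRI,** rename the outcome 'time to combined radiological and clinical healing' and state that it does not by itself support a claim of clinical benefit. That claim then rests on pain, SF-36 and time to discharge. Cost: wording only, though those outcomes are collected in an open-label trial.

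In either case, reconcile 'unhealed' in Fig. 2 footnote 1 with footnote 5, saying whether it is meant radiologically or clinically. The same footnote also governs how long treatment continues, so the choice of meaning is for the sponsor and clinical team.

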##### Time to discharge from Army physical rehabilitation

The time from randomisation to the initial decision to discharge from Army physical rehabilitation will be obtained from participants’ Army medical records. A review by an exercise rehabilitation instructor, physiotherapist and general practitioner will determine when a recruit will be discharged from physical rehabilitation and is, therefore, considered to be fully fit and ready to return to training.

##### Pain symptoms

Participants will rate the level of pain they are feeling on a visual analogue scale once-a-week for the duration of their participation in the study [42, 43]. Pain scores will be analysed as a change from baseline.

##### Health-related quality of life

The Short Form (36) Health Survey (SF-36) will be completed by participants at baseline and every 4 weeks for the duration of their participation in the study to assess their health-related quality of life [44, 45]. The SF-36 is a self-administered 36-item questionnaire that measures health-related quality of life in eight domains (vitality, physical functioning, bodily pain, general health perceptions, physical role functioning, emotional role functioning, social role functioning, and mental health). Each domain is scored from 0 to 100 (lowest to highest level). Physical and mental summary scores will be obtained by aggregating scores across domains and analysed as a change from baseline.

##### Adverse events

Any unfavourable and unintended sign, symptom or illness that develops or worsens during an individual’s participation in the study, and for 4 weeks afterwards, will be recorded and classified as an adverse event (see the “Adverse event reporting and harms {22}” section).

#### Exploratory outcomes

##### Blood and urine biochemistry

Blood and urine samples will be collected at baseline and weeks 4, 8, 12 and 16. Where a fracture remains unhealed at week 16, additional blood and urine samples will be collected at weeks 20 and 24. Venous blood samples will be collected from an antecubital vein. The NHS institution laboratory will analyse blood and urine samples for safety (Table 1). Aliquots of serum, plasma and urine will be stored at − 80 °C, before being defrosted prior to research analyses (Table 1). Analytes will be analysed as a change from baseline. All blood and urine biochemical analyses will be completed by technicians blind to the randomisation outcome.

Slight and transient elevations of serum calcium concentration are normal following the injection of teriparatide. It takes 4–6 h for serum calcium to reach C_max_ and 16–24 h to return to baseline after each dose [24]. Therefore, blood samples will be collected at least 16 h after a participant’s most recent teriparatide injection. Where their regular dosing regimen means treatment would be interrupted to comply with this, the time of their last dose will be recorded. In the event of a hypercalcemia result, a trough measurement will be made within 7 days, before any dose modifications or discontinuations are made. Randomisation will be permitted prior to the receipt of baseline plasma parathyroid hormone concentration. However, in the unlikely event of a participant presenting with a plasma parathyroid hormone concentration outside the adult reference range, they will be called back for review and instructed to stop injecting teriparatide.

##### Bone density and morphology

Bone density will be assessed at the lumbar spine and hips by dual-energy X-ray absorptiometry (DXA) at baseline and week 16 (Lunar iDXA, GE Healthcare, Buckinghamshire, UK). Bone density and morphology will be measured by peripheral quantitative computed tomography (pQCT) scans of the diaphyseal tibia (XCT2000L, Stratec, Pforzheim, Germany), and high-resolution pQCT (HR-pQCT) scans of the metaphyseal tibia and radius (Xtreme CTII, Scanco Medical, Bruttisellen, Switzerland) at baseline and week 16, and week 24 where a fracture remains unhealed at week 16. Bone density and morphology will be analysed as a change from baseline. The non-dominant arm and non-fractured, non-dominant leg will be scanned where possible. A random sample of analysed images (≥ 10%) will be reviewed at the end of the study by an independent assessor blind to the randomisation outcome.

##### Physical activity levels

A wrist-mounted tri-axial accelerometer will be worn by a subgroup of participants for the duration of their participation in the study to assess their physical activity levels. A minimum of 10 participants in each of the control and intervention arms will wear an accelerometer.

##### Long-term future fracture rate

Participants’ Army medical records will be reviewed for 5 years after their final study visit to record any subsequent bone injuries and fractures.

##### Confounding variables

Participants’ alcohol consumption and smoking habits (confounding variables for skeletal health [46]) will be recorded at baseline and every 4 weeks for the duration of their participation in the study. Participants’ physical fitness will be recorded by accessing their Army fitness records.

### Participant timeline {13}

A summary schedule of study enrolment, interventions and assessments is given in Fig. 2.

**Fig. 2 Fig2:**
[figure not shown]
Schedule of study enrolment, interventions and assessments. ^1^Intervention and assessments to continue after week 16 only where fractures are unhealed at week 16; ^2^Serum 25-hydroxyvitamin D < 30 nmol/L, deficient; ≥30 nmol/L, not deficient; ^3^Daily subcutaneous injection (20 μg/day); ^4^Magnetic resonance imaging (MRI) scans to cease when fracture is radiologically healed; ^5^Clinical assessments twice weekly after fracture is radiologically healed, and to cease when fracture is clinically healed; ^6^Weekly visual analogue scale; ^7^Short Form (36) Health Survey; ^8^Adverse events recorded for 4 weeks after participant’s final study visit (i.e. until weeks 20 or 28). ^9^Safety and research blood biochemistry; ^10^Safety and research urine biochemistry; ^11^Dual-energy X-ray absorptiometry (DXA) scan of the lumbar spine and hips (allocation and week 16 only); peripheral quantitative computed tomography (pQCT) scan of the diaphyseal tibia; and high-resolution pQCT (HR-pQCT) scan of the metaphyseal tibia and radius; ^12^Accelerometer worn 24 h/day and replaced four-weekly; ^13^Review of Army medical records for 5 years after participant’s final study visit; ^14^Columbia-Suicide Severity Scale for all at allocation, and four-weekly for participants allocated to the intervention arm; ^15^Review of Army fitness records; ^16^Pregnancy test for all at allocation, week 16 and 24, and four-weekly for participants allocated to the intervention arm

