**Fig. 1 Fig1:**
[figure not shown]
Overview of the trial design, interventions and assessments. ^1^Serum 25-hydroxyvitamin D < 30 nmol/L, deficient; ≥30 nmol/L, not deficient; ^2^Pregnancy test for all at baseline, week 16 and 24, and four-weekly for participants allocated to the intervention arm; ^3^Weekly visual analogue scale; ^4^Short Form (36) Health Survey; ^5^Dual-energy X-ray absorptiometry (DXA) scan of the lumbar spine and hips (baseline and week 16 only); peripheral quantitative computed tomography (pQCT) scan of the diaphyseal tibia; and high-resolution pQCT (HR-pQCT) scan of the metaphyseal tibia and radius; ^6^Accelerometer worn 24 h/day and replaced four-weekly; ^7^Columbia-Suicide Severity Rating Scale (C-SSRS) for all at baseline, and four-weekly for participants allocated to the intervention arm; ^8^Review of Army fitness records; ^9^Magnetic resonance imaging (MRI) scans to cease when fracture is radiologically healed; ^10^Clinical assessments twice weekly after fracture is radiologically healed, and to cease when fracture is clinically healed; ^11^Review of Army medical records

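### Repeat C-SSRS screening in the teriparatide arm only makes depression and suicidality events non-comparable between arms; a lesser point is that follow-up after week 16 depends on healing

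*Protocol article*

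**What the plan says.** **Screening.** Fig. 1, footnote 7, schedules the "C-SSRS) for all at baseline, and four-weekly for participants allocated to the intervention arm". Fig. 2, footnote 14, agrees: "for all at allocation, and four-weekly for participants allocated to the intervention arm". Criteria for discontinuing {11b} ties the repeat screen to re-dispensing of the drug. The Safety part of the Discussion says mood is monitored because depression may be an unwanted effect of teriparatide.

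**Adverse events.** These are a secondary outcome. Anything unfavourable that develops or worsens "during an individual’s participation in the study, and for 4 weeks afterwards, will be recorded and classified as an adverse event". Adverse event reporting and harms {22} exempts no category of event. Trial design {8} states that the trial is open label.

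**Contact.** Under Plans to promote retention {18b}, participants in both arms see investigators at least once every four weeks. Under Plans for assessment {18a}, investigators ask participants about adverse events.

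**Length of follow-up.** Fig. 2, footnote 1: "Intervention and assessments to continue after week 16 only where fractures are unhealed at week 16". Footnote 8 sets the end of adverse-event recording at four weeks after the "final study visit (i.e. until weeks 20 or 28"). Pain is rated "on a visual analogue scale once-a-week for the duration of their participation in the study". The SF-36 is completed "at baseline and every 4 weeks for the duration of their participation in the study to assess their health-related quality of life". Both are analysed as change from baseline.

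**The concern.** An adverse-event comparison is fair only if both arms are looked at equally hard and for equally long.

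The first condition fails for one class of event. Participants on teriparatide are put through a structured questionnaire on suicidality every four weeks, and controls are not. Anything the questionnaire brings up counts as an adverse event, because none is exempt. The extra events would fall in the teriparatide arm and concern the effect the protocol itself suspects, so a false safety signal could result. The open label adds to this, since unprompted reporting may also differ between people who know they are on the drug and people who know they are not.

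The second condition can fail after week 16. Who is followed further depends on healing, which the drug is meant to speed up. If it does, controls are observed longer for adverse events, and the pain and SF-36 data from weeks 17 to 24 come from a slower-healing remainder selected differently in each arm. This would make teriparatide look slightly safer, the opposite direction to the screening problem.

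**Working it through.** **1. The plan's own figures.** Final visit plus four weeks: 16 + 4 = 20 and 24 + 4 = 28. Both match Fig. 2, footnote 8.

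**2. Number of structured screens.** Teriparatide is dispensed in four-week supplies (Intervention description {11a}). Sixteen weeks is 16/4 = 4 supplies, hence 3 re-dispensings after the first; twenty-four weeks is 24/4 = 6 supplies, hence 5. With a screen before each, a participant who stays on treatment has at least 3 to 5 post-baseline screens. A control has none.

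**3. Effect of one-arm screening when true rates are equal.** Let *d* be the fraction of screen-detectable events that general questioning alone would catch. Taking the screened arm to catch all of them, the apparent ratio (teriparatide/control) is 1/*d*. The documents give no value for *d*, so it is assumed:

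- *d* = 0.8: 1/0.8 = 1.25
- *d* = 0.5: 1/0.5 = 2.0
- *d* = 0.3: 1/0.3 = 3.3

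This applies only to depression and suicidality events, not to adverse events as a whole.

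**4. Length of adverse-event follow-up.** Let *u* be the proportion unhealed at week 16. Mean scheduled window = 20 + 8*u* weeks. For the crude proportion with at least one event, assume the same constant hazard in both arms and a risk *R* by week 20. The risk by week 28 is then 1 − (1 − *R*)^1.4, because 28/20 = 1.4. For *R* = 20% this is 26.8%; for *R* = 50% it is 62.1%. The whole-period risk in an arm is (1 − *u*) × risk to week 20 + *u* × risk to week 28.

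The article gives no week-16 healing rates, so *u* is assumed. The 57%/29% row borrows the week-8 non-success rates from Sample size {14} (100 − 43 and 100 − 71) purely as an illustration.

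| Unhealed, control / teriparatide | Mean window (weeks) | Control ÷ teriparatide | Crude risk ratio (teriparatide/control), *R* = 20% | *R* = 50% |
|---|---|---|---|---|
| 10% / 5% | 20.8 / 20.4 | 1.02 | 0.984 | 0.988 |
| 20% / 10% | 21.6 / 20.8 | 1.04 | 0.968 | 0.977 |
| 40% / 20% | 23.2 / 21.6 | 1.07 | 0.940 | 0.956 |
| 57% / 29% | 24.6 / 22.3 | 1.10 | 0.920 | 0.940 |
| 30% / 30% | 22.4 / 22.4 | 1.00 | 1.00 | 1.00 |

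Example, last unequal row, *R* = 50%: control 0.43 × 0.50 + 0.57 × 0.621 = 0.569; teriparatide 0.71 × 0.50 + 0.29 × 0.621 = 0.535; ratio 0.940, difference 3.4 percentage points. That is the largest difference in the table.

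**5. Who has pain and SF-36 data after week 16.** Using the 54 per arm that the protocol expects after 20% drop-out by week 8, the 57%/29% row leaves about 31 controls and 16 on teriparatide; the 20%/10% row leaves about 11 and 5. Up to week 16 the schedule is the same for everyone.

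**The case against.** **The C-SSRS is a dispensing check, not an outcome.** It is not among the listed outcomes, and controls have nothing dispensed. This is correct and explains why treated participants are screened. It does not make the resulting adverse-event counts comparable, because what the screen finds enters an outcome that is compared.

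**Controls are not unobserved.** They are asked about adverse events, are seen at least four-weekly, and complete the SF-36 with its mental-health domain. Entry screening with the C-SSRS also removes depression in both arms. All of this narrows the gap, and it is why *d* above is not zero. None of it is a structured question on suicidality.

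**Longer recording in the unhealed has a reason.** Injections continue to week 24 in unhealed treated participants, so recording to week 28 covers exposure plus four weeks. This stands; the data should be collected.

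**No faulty analysis is stated.** A reader might infer that the adverse-event, pain and SF-36 comparisons as a whole are not like for like, or that crude proportions are bound to favour teriparatide. The documents do not support either. One rule governs both arms, and the scheduled length is equal to week 20 for adverse events and to week 16 for pain and SF-36. The article announces neither a crude whole-period comparison nor a contrast at weeks 17 to 24. Statistical methods {20a} leaves the models to a statistical analysis plan (SAP) that is not shown and may already use a common window. If healing at week 16 is equal, the windows are equal too.

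**Conclusion.** The main point holds. Following the protocol as written gives unequal ascertainment of depression and suicidality events, a suspected drug effect within a secondary outcome. The bias runs against teriparatide. Its size is unknown: 1.25 to 3.3 as an apparent ratio under no true effect, for general questioning that catches 80% down to 30% of screen-detectable events. This is a data-collection defect that the SAP cannot repair.

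The window point is secondary and conditional. It concerns only whole-period adverse-event totals and pain and SF-36 data after week 16, and only if healing at week 16 differs between arms. On the assumed rates, controls have 2–10% longer adverse-event follow-up, and the crude risk ratio under no effect is about 0.92–0.99. The absence of a common window from the article is not itself an error, since the SAP can set one.

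Comparisons within the common windows and the week-8 primary outcome are unaffected.

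**What to change.** **Screening.** Give the C-SSRS to controls at the four-weekly contacts they already attend. Cost: a short questionnaire and a protocol amendment. How a positive screen in a control is handled clinically is for the trial's clinicians. Recruitment is already under way, so some controls will have passed visits without a screen. For that reason, and as the fallback if controls are not screened, record for each depression or suicidality event whether the C-SSRS or general questioning found it. Show screen-detected events separately from those found by the questioning common to both arms. This costs one extra data field. The events stay reported, but outside the between-arm comparison.

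**Windows.** State in the SAP that the between-arm comparison uses adverse events to week 20 and pain and SF-36 to week 16. Report later adverse events per person-time, and later pain and SF-36 data descriptively. Cost: a few lines of SAP text, and late events in unhealed participants sit outside the main comparison. After week 16, healed participants are past their final visit while unhealed ones still attend, so a count of adverse events to week 16 is a useful check on the week-20 result.
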